**Ankle-foot orthoses (AFOs).**

AFOs are often necessary to overcome mobility limitations related to lower limb neuromusculoskeletal injury. The availability of orthotic options for improving function is expanding, but still limited [5]. Relative to the field of prosthetics, orthotics research and development has remained relatively understudied and underfunded for decades. Moreover, outcomes are better for individuals who have sustained lower limb amputation than for those who have had their limb salvaged or reconstructed [6], which is potentially due to specialized technology available and provided to those with amputation, and not to those with limb salvage [6]. To date, a wealth of information on comparative effectiveness of designs, standardization of certain outcome measures, and surveys exist to identify the needs and preferences of prosthesis users, but the same level of scientific evidence does not exist for AFO users. The current evidence is insufficient to develop Clinical Practice Guidelines. Despite the lack of scientific evidence, Medicare expenditures for orthotics in 2016 reached $1 billion [7]. A 2015 National Commission on Orthotic and Prosthetic Education (NCOPE) study projected that by the year 2025, the number of certified orthotists will need to increase by 90% to meet future patient demands [8]. There is a critical need to better optimize orthotic devices for patients and provide evidence-based tools for clinicians. The proposed study with its unique test-drive strategy will address these unmet needs by optimizing the process of selecting an AFO in a patient-centered and patient-specific manner.

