# Objectives

The overarching goal of this research is to optimize mobility, function and satisfaction for Service members, Veteran, and civilian AFO users with lower limb musculoskeletal injuries. To achieve this, our primary purpose is to determine the extent to which a ‘test-drive’ strategy, using an AFO emulator, can be used to predict device function, mobility and preference outcomes with corresponding commercially available (*actual*) AFOs in Service members and Veterans with lower limb musculoskeletal trauma.

**Specific Aim 1**: Test the ability of the AFO emulator to reproduce the user experience of wearing *actual* AFOs during different in-lab activities (walking, running, stair climbing; level ground, ramps) in individuals with lower limb musculoskeletal injury. This aim will determine if the proposed AFO emulator framework can provide an option for quickly exploring multiple devices in a short period of time.

**Research Question 1a**: Do self-reported measures of preference differ between *emulated* and corresponding *actual* AFO conditions?

**Hypothesis 1a**: Preference scores for *emulated* AFO conditions will be strongly correlated with preference for the corresponding *actual* AFO.

**Research Question 1b**: Do measures of performance and self-reported outcomes differ between *emulated* and *actual* AFOs conditions?

**Hypothesis 1b**: Measures of performance and self-reported outcomes in the *emulated* AFO condition will be strongly correlated with those using corresponding *actual* AFOs.

**Specific Aim 2*:*** Test the ability of a short-term, in-laboratory evaluation of function, mobility, and preference to predict those same outcomes longer-term (i.e., after 2 week use in the community) in AFO users with lower limb musculoskeletal injury. This aim will determine the predictive ability of a brief test-drive strategy using *actual* and *emulated* AFOs to identify function, mobility, satisfaction, and preference at follow-up after two weeks of use in the community environment with corresponding *actual* AFOs.

**Research Question 2a**: Do measures of user preferences identified during a brief test-drive session with an *emulated* AFO predict user preferences after the *actual* AFO is worn longer-term in the community environment?

**Hypothesis 2a**: Initial preference scores for each *emulated* AFO will be strongly correlated with preference for the corresponding *actual* AFO at follow-up.

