| Walking on a level treadmill at 3 standardized speeds based on leg length [23] |
| Walking uphill on a treadmill at a comfortable speed |
| Walking downhill on a treadmill at a comfortable speed |
| Walking up a stairmill at a comfortable pace (optional) |
| Running on a treadmill at a comfortable speed (optional) |

**Table 1.** Activities trial conditions

During the activities trials we will collect gait biomechanics. Participants will be asked to change into a tight-fitting shirt and shorts that we can provide. A private area for participants to change clothes will be provided. We will record a series of standard body measurements such as height, weight, and lengths of segments. We will attach up to 70 reflective makers using double sided tape and wrap to the participant’s body segments and joints. During the tests in the lab, the cameras will record the location and movement of the markers; they do not record a picture of the body. Ground reaction force data will be collected from an instrumented treadmill during treadmill walking.

**Patient-Reported Outcomes.** Participants will complete a series of questionnaires to assess patient-reported outcomes. Some of the questions in these instruments are not sensitive to a short-term trial and may be excluded or modified (see descriptions below).

• **AFO Preference**. Preference is the primary outcome measure. Preference for a given condition will be assessed using a 10-point scale ranging from “Do not like at all” to “Like very much”. Each participant will be asked to rate his or her preference during each specific trialed activity. During in-lab testing, preference will be assessed at the conclusion of the Activities Trial. Additional information of the user’s assessment of the AFO stiffness ranging from “Far too stiff” to “Far too soft” and whether they would wear the device on a daily basis will be collected.

• **AFO Comparison**. Ranked preference and perceived AFO stiffness will be collected at the actual and emulated in-lab session between the three braces trialed and following the third community take home trial.

• **Rating of Perceived Exertion** (RPE). RPE will be recorded on a CR 10 Borg scale [24, 25]. RPE will be recorded after each activity in the Activities Trial and after the 2-Minute Walk Test (see below).

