## 4.6 Data Analysis

**Aim 1.** The purpose of Aim 1 is to test the ability of the AFO emulator to reproduce the user experience of wearing actual AFOs during different activities (walking, running, stair climbing; level ground, ramps) in individuals with lower limb musculoskeletal injury. We will consider the outcome measures as continuous response variables in the statistical analysis. We will evaluate the data from the in-lab actual and in-lab *emulated* sessions using a linear mixed effect (LME) regression with the *emulated* AFO data as the independent fixed effect, the *actual* AFO data as the dependent fixed effect, and subject participant as a random intercept.

**Hypothesis 1A**. In Specific Aim 1A, we are testing the hypothesis that the experimental AFO preference measured during the in-lab *emulated* session will be significantly correlated with the experimental AFO preference measured during the in-lab *actual* session. This model estimates a change in *actual* AFO preference per unit change of *emulated* AFO preference.

**Hypothesis 1B**. In Specific Aim 1B, we are testing the hypothesis that self-reported measures and biomechanics will be significantly correlated between the in-lab *emulated* session and the in-lab *actual* session. This model operates the same as in 1A, substituting measures of function and mobility for preference.

**Aim 2.** The goal of Aim 2 is to determine if the in-lab (*emulated* and *actual*) measurements are a good predictor of the longer-term measurements made following a take home trial. To perform this analysis, we compute a similar LME regression as Aim 1 with the *emulated* *or actual* in-lab AFO data as the independent fixed effect, the *actual* take-home trial AFO data as the dependent fixed effect and subject participant as a random intercept.

**Hypothesis 2A**. In Specific Aim 2A, we are testing the hypothesis that the experimental AFO preference measured during the in-lab *emulated* session will be significantly correlated with the experimental AFO preference measured during the take home-trials. This model operates the same as in 1A, substituting measures of take-home trial preference as the dependent variable.

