**Hypothesis 2B**. In Specific Aim 2B, we are testing the hypothesis that the experimental AFO preference measured during the in-lab *actual* AFO session will be significantly correlated with the experimental AFO preference measured during the take home-trials. This model operates the same as in 1A, substituting measures of take-home trial preference as the dependent variable.

**Hypothesis 2C**. In Specific Aim 2C, we are testing the hypothesis that measures of preference will be significantly correlated between the *emulated* in-lab session and measures of performance and self-reported measures of mobility at the take-home trials. This model operates the same as in 2A, substituting measures of performance and self-reported outcomes for preference as the dependent variable.

**Hypothesis 2D**. In Specific Aim 2D, we are testing the hypothesis that measures of preference will be significantly correlated between the *actual* in-lab session and measures of performance and self-reported measures of mobility at the take-home trials. This model operates the same as in 2A, substituting measures of performance and self-reported outcomes for preference as the dependent variable.

**Power Analysis for Aims 1 & 2**. Our power analysis is based upon pilot data collected for a similar study using prosthetic feet which tested mobility and preference for three participants and two feet between *emulated* and *actual* sessions. Based upon the estimates of slope and residual error from the pilot data, 10,000 datasets were created for a sample size of N=50. Power, estimated as the proportion of datasets that rejected the null hypothesis of a slope equal to zero, was 97% for the preference scores and 98% for the mobility scores. To account for a 12% dropout rate (note that prior prosthetic emulator study experienced a 7% dropout rate) a total sample of N=56 participants will be tested.

**Exploratory Aim**. In this exploration, participants will be allowed to dynamically “dial-in” and change in the stiffness settings of the emulator device so that they design an optimal device to meet their needs. The *emulated* device will then be compared to the device that was clinically prescribed for them as part of usual care. To test the hypothesis a simple paired t-test will be used which compares the preference means and other outcomes measures of the patient-optimized and clinician-optimized conditions.

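### The planned slope mixes rating style with device discrimination, so 1A, 2A and 2B can reach significance without showing that the in-lab session tells a participant's AFOs apart

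*Protocol*

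**What the plan says.** Section 4.6 of the protocol sets out the Aim 1 model. The emulated score is the predictor, with the actual "AFO data as the dependent fixed effect, and subject participant as a random intercept". The slope is read as the change in actual preference for each unit of emulated preference. For Aim 2 the protocol states "we compute a similar LME regression as Aim 1", with the emulated or actual in-lab score as predictor and the take-home score as outcome. No split of the predictor into participant mean and deviation is described, and no AFO term.

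Success for 1A is that emulated preference "will be significantly correlated with the experimental AFO preference measured during the in-lab" actual session. The power paragraph confirms the null: "Power, estimated as the proportion of datasets that rejected the null hypothesis of a slope equal to zero".

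The Objectives section puts the question device by device. Hypothesis 1a says that preference scores for emulated "AFO conditions will be strongly correlated with preference for the corresponding" actual AFO; 2a and 2b have the same form at follow-up. Preference is the primary outcome and is a subjective rating: "Preference for a given condition will be assessed using a 10-point scale ranging from" strong dislike to strong liking (section 4.5). Each participant rates three AFOs.

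**The concern.** With three ratings per participant in each session, emulated and actual scores can be associated in two ways. Between participants, those who score everything high in one session may score everything high in the other. Within participants, the AFO rated above a person's own average when emulated may be rated above that average when worn. A test-drive helps choose among devices only if the second holds.

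A random intercept does not isolate the second. It assumes that a participant's intercept is unrelated to the predictor, and rating style carried across sessions breaks that assumption. The slope is then pulled towards the between-person association. The primary-outcome hypotheses 1a, 2a and 2b could be declared confirmed although the in-lab session did not separate a participant's three AFOs. The Introduction describes the purpose as "optimizing the process of selecting an AFO in a patient-centered and patient-specific manner", so that is the conclusion readers would draw.

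**Working it through.** **Inputs from the protocol (sections 4.5 and 4.6).** Three AFOs per participant; N = 50 in the power simulation; random-intercept model on the score; null slope zero. Alpha and sidedness are not stated, so two-sided 5% is assumed.

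**The plan's own figure.** The stated power is 97% for preference and 98% for mobility. It cannot be reproduced, because the pilot slope and residual error (three participants, two prosthetic feet) are not given.

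**Assumed inputs.** The protocol gives neither the share of score variance due to the person (ICC) nor the correlation of the person effect between sessions (rho). Both are varied below. The true within-person slope is set to exactly zero.

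**Why the slope is a blend.** With k ratings per person and λ the ratio of intercept variance to residual variance,

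slope = (Wxy + t·Bxy) / (Wxx + t·Bxx), where t = 1/(1 + kλ),

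and W and B are the within-person and between-person sums of squares and products. The between-person part drops out only if t = 0.

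Worked case with ICC 0.5, rho 0.7 and total variance 1:
- Wxx = 50 × 2 × 0.5 = 50, and Wxy = 0 by assumption.
- Bxx = 3 × 49 × (0.5 + 0.5/3) = 98.
- Between-person slope = 0.7 × 0.5 / (0.5 + 0.5/3) = 0.525, so Bxy = 98 × 0.525 = 51.5.
- Try slope 0.20. Residual within-person variance = 0.5 × (1 + 0.04) = 0.52. Residual person variance = 0.5 × (1 − 0.28 + 0.04) = 0.38. So λ = 0.38/0.52 = 0.73 and t = 1/(1 + 2.19) = 0.313.
- Slope = 0.313 × 51.5 / (50 + 0.313 × 98) = 16.1/80.7 = 0.20, which agrees with the trial value.
- SE = √(0.52/80.7) = 0.080, so z is about 2.5 and rejection about 70%.

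Simulation of the same case gives a mean slope of 0.20 and rejection in 68% of trials.

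**Rejection at a true within-person slope of zero** (50 × 3, REML, person and within-person SDs in scale points; ranges cover the SDs shown and repeat runs):

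| Cross-session correlation | Person SD | Within-person SD | Planned test | Centred slope |
|---|---|---|---|---|
| 0 | 1-2 | 1.5-2 | about 5% | about 5% |
| 0.3 | 1 | 1.5 | 10-12% | about 5% |
| 0.6 | 1-2 | 1.5-2 | 18-66% | about 5% |
| 1.0 | 1-1.5 | 1.5-2 | 48-97% | about 5% |

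By ICC, at rho 0.7 and rho 1.0 respectively: ICC 0.1, 12% and 19%; ICC 0.2, 26% and 49%; ICC 0.3, 42% and 75%; ICC 0.5, 68% and 97%. Scores rounded and bounded to 1-10 behave alike: 43% (ICC 0.31, rho 0.7), 67% (ICC 0.50, rho 0.7) and 96% (ICC 0.50, rho 1).

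**Power of the centred test.** At ICC 0.5 and rho 0.7, power is 52%, 87% and 99% for assumed standardised within-person slopes of 0.2, 0.3 and 0.4. At 0.2 the planned blended test rejects in 99% of trials, so power in the high nineties for the blended slope can coexist with about 52% for the within-person slope.

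**The case against.** The strongest reply is that a non-zero blended slope is not a type I error against the null the protocol wrote. The model answers a broader question, and part of Aim 2 is broad: section 4.6 asks whether in-lab measurements predict longer-term ones, which includes knowing which participants will do poorly. This stands for 2C and 2D, whose outcomes include timed and distance tests that rating style cannot move. It does not rescue 1A, 2A and 2B, which are worded around preference for the corresponding AFO.

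Second, the size rests on assumed variance components, and with no shared leniency the test keeps its 5% level. This stands. Shared rating style can produce a significant slope; the protocol does not show that it will.

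Third, centring might be left to a SAP. The protocol nevertheless fixes the predictor, the random structure, the reading of the slope and the null, and a split of the predictor would change the coefficient tested.

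Fourth, ranked preference among the three AFOs is collected at both in-lab sessions and after the third community trial. Complete, untied ranks have the same mean for everyone, so leniency cannot enter. That is a useful check, but section 4.6 assigns the ranks no analysis of their own.

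A reader might also infer that average AFO differences create a spurious result: if everyone dislikes one device in both settings, the slope is positive. The protocol does not support calling this a false positive. Aim 1 is to reproduce the experience of wearing the actual devices, and a device that is unpopular both emulated and worn has been reproduced. Centring would not remove that signal, nor should it for Aim 1.

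**Conclusion.** The point holds for 1A, 2A and 2B. The planned slope does not separate rating style from device discrimination, and a significant result could come from the former alone. With no within-person association, rejection runs from about 5% (no shared leniency) through 10-12% and 18-66% to 48-97% (leniency fully shared). These figures assume 50 participants with three AFOs each, a two-sided 5% test and the SDs listed above; none of the variance inputs comes from the protocol.

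Three stronger readings are not supported: that the planned test is bound to mislead, that the between-person association is irrelevant to every hypothesis, and that the stated power is wrong. The 97% and 98% are not shown to apply to the within-person slope, which is a narrower statement.

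**What to change.** In section 4.6:

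- Split the in-lab preference score into each participant's mean and the deviation from that mean. Test 1A, 2A and 2B on the deviation slope, and report the between-person slope separately.
- For 1B, 2C and 2D, report both slopes without making the within-person slope the sole criterion.
- Add a secondary model with AFO (device 1, 2 or 3) as a fixed effect, used only to support a claim that the test-drive gives patient-specific information beyond average device differences. The collected rankings can serve as a supporting check.
- Rerun the power simulation for the within-person slope, stating the slope, the variance components and alpha.

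The change needs no new data and no change in conduct. Its cost is information: of 50 × 3 = 150 ratings, removing 50 participant means leaves about 100 units for the within-person test. If the true standardised within-person slope is near 0.2, power is only about 52%. The change should be made before the data are analysed, because afterwards it would be post hoc.

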## 4.5 Study Evaluations

Prior to enrolling and consenting, participants must meet the inclusion criteria described above. Once consented, AFOs will be fit to each subject at an initial visit, based on manufacturer recommendations for foot size and body weight. Additional fitting sessions may be utilized to ensure a good fit to the individual for all three actual AFOs to be evaluated.

Participants will undergo up to three in-lab sessions: testing the emulated AFOs, testing the actual AFOs, and an optional exploratory aim session of user-selected AFO properties. Participants will undergo three 2-week periods where participants will be instructed to wear the study AFO instead of their clinically-prescribed AFO for all usual activities of daily living. After two weeks of wearing each AFO, participants will return to the laboratory for follow-up evaluation (Figure 1). Injury history and participant demographics will be collected at the initial intake session.

Participants will be block randomized to ensure similar numbers of participants are assigned to each of three AFO testing sequences and similar numbers of participants undergo either the emulated in-lab session or actual AFO in-lab session first.

**Emulated AFO testing session**. Participants will begin by walking on a treadmill in the emulator to become accustomed to its use. Participants will wear the emulator’s end effector the way they would their clinically prescribed AFO and the study orthotist will be present to make any necessary adjustments. The emulator parameters will be adjusted by the research staff member in real-time as the subject walks so they experience the range of emulated AFO conditions to be tested. After the emulator accommodation period, participants will trial three emulated AFOs in a randomized order. Participants will complete an Activities Trial and patient reported outcomes (described below).

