**Actual AFO testing session.** Prior to the start of the testing session, participants will be fit with the three actual AFOs to be worn during the data collection. Fitting will be done according to the routine standard of clinical care (e.g. test device for the custom AFOs). On the day participants complete the actual AFO testing, they will walk on the treadmill in each AFO condition to acclimate prior to testing. Then, participants will undergo the same Activities Trial as in the emulated AFO testing session (described below). The same questionnaires will be completed to identify patient-reported outcomes. In the actual AFO testing session, participants will additionally complete a series of performance tests described below.

**Two-week follow up sessions**. Participants will complete two-week long community trials in each of the three actual AFO conditions in a randomized. AFOs will have already been fit to each subject as described above. Participants will be instructed to wear the study AFO instead of their clinically-prescribed AFO for all usual activities of daily living. After two weeks of wearing each AFO, participants will return to the laboratory for follow-up evaluation; Patient-Reported Outcomes and Performance Tests will be assessed. A subset of participants may also have the activities trial collected and/or gait biomechanics collected at the two-week follow up sessions.

**The Exploratory Session** will compare a participant’s clinically prescribed AFO (clinician optimized) to a participant-optimized setting on the emulator. Stiffness will be the optimized parameter. In this exploration, participants will be allowed to dial in and change the stiffness parameters on the emulator so that they self-identify an optimal value (patient-optimized).

**Figure 1.** Study Overview

**
[figure not shown]
**

**Activities Trial**. The activities selected are intended to represent a range of activities commonly encountered in the community environment (Table 1). As detailed below, activities will be assigned in a manner specific and appropriate to the individual patient (e.g., participants of a lower mobility or with contraindications will not be asked to run). Each speed and activity condition will take place for at least 30-seconds and rest will be provided between activities as needed. After each AFO condition is complete, participants will rest for at least 10 minutes before engaging in the next AFO condition.

| **Activities Trial** |
| --- |

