***Potential Risks to Participants*** There is a risk of injury or physical discomfort associated with the device casting, fitting, wear, or testing during study participation. Wearing the emulated AFO may also cause discomfort. There is always the risk that the emulator could fail or stop working properly. This could cause minor soft tissue injury (i.e. soreness, bruising) or other minor injury (i.e. knee or ankle joint soreness). There are built-in emergency stops designed to prevent injury and Humotech currently has 15 emulator systems in use with no reported safety concerns. The risks of the emulator are similar to those of wearing the actual AFO. These risks are considered minimal risks since the activities are consistent with those performed during physical therapy evaluations or AFO fittings, and the devices can be removed at the participant’s discretion. Device fittings will be overseen by a certified prosthetist-orthotist and data collection will be conducted by trained research staff. Furthermore, if a participant cannot safely perform a test once begun, the test will be stopped and the participant will proceed to the next test or try again. If the participants experience any pain or discomfort during or after testing, they will be instructed let the research staff know. Participants may experience fatigue during the assessment sessions. If fatigued, participants will be instructed inform research staff and will be allowed to rest until they are comfortable or decide to discontinue.

There is always the possibility that participants may fall while walking in an AFO but procedures have been put in place to minimize this risk. All study interventions are non-invasive. There may, however, be unforeseen risks associated with this study.

Some of the questionnaires may make participants feel uncomfortable or embarrassed. This is not expected based on the nature of the study, but if they experience these emotions they can decline to answer the questions.

Although we make every effort to keep participants information secret, there is always a chance of loss of confidentiality through someone gaining access to the information that researchers have collected. Section 16 outlines how we will protect your privacy to the best of our ability.

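### The Aim 1 and Aim 2 models omit the randomised test position, and the protocol does not say whether one device order is kept across stages, which decides whether order trends bias the slope or only cost power

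*Protocol*

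**What the plan says.** Section 4.6 (Aim 1) writes the model out: the emulated score is the single fixed predictor, with the actual "AFO data as the dependent fixed effect, and subject participant as a random intercept". For Aim 2, "we compute a similar LME regression as Aim 1", with the take-home score as response; Hypotheses 2A to 2D only exchange variables. The power paragraph shows that the test is rejection of a zero slope.

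Section 4.5 describes the ordering:

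- **Overall:** "Participants will be block randomized to ensure similar numbers of participants are assigned to each of three AFO testing sequences". Which in-lab session comes first is also balanced. That is a between-participant factor, separate from the within-participant trend at issue here.
- **Emulated session:** "participants will trial three emulated AFOs in a randomized order".
- **Actual in-lab session:** "they will walk on the treadmill in each AFO condition to acclimate prior to testing"; no order is stated for the testing itself.
- **Community trials:** described as randomised, but the sentence breaks off before saying what is randomised.

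Under potential risks, section 4.5 also notes: "Participants may experience fatigue during the assessment sessions". It provides at least 10 minutes of rest between AFO conditions.

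**The concern.** Each participant contributes three scores per stage, taken in sequence. Ratings may drift over position through fatigue within a session, or through adaptation over three consecutive two-week periods in people who may have as little as two weeks of AFO experience. A model without position cannot separate such drift from a real link between emulated and actual scores.

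If a participant meets the devices in the same order at both stages, position is a common cause of predictor and outcome. A slope can then appear, or be hidden, for reasons unrelated to the emulator. If the orders differ at random, drift is extra noise in both scores. Preference is the primary outcome and a non-zero slope is the evidence sought, so either effect bears on the main claim.

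**Working it through.** **Inputs from the protocol.** N = 50 evaluable participants (section 4.6; 50 × 1.12 = 56 reproduces the recruitment target), three AFOs per stage, three sequences, random-intercept model, test of slope = 0. The stated power of 97% and 98% cannot be reproduced, because the pilot slope, the residual error and alpha are not given.

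**Assumptions.** Two-sided alpha 0.05; a linear drift of *d* within-person SD per position at both stages; participant SD equal to residual SD.

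**Direction of bias, same order.** Code position as −1, 0, 1; its within-person sample variance is (1 + 0 + 1)/2 = 1. With drifts d₁ (predictor) and d₂ (outcome) and no true relation, the within-person slope is

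d₁d₂ / (1 + d₁²).

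- d₁ = d₂ = 0.25: 0.0625/1.0625 = 0.06.
- d₁ = d₂ = 0.5: 0.25/1.25 = 0.20.
- d₁ = 0.5, d₂ = −0.5: −0.20.

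The random-intercept estimate also uses between-person information, which carries no relation here, so the simulated mean slopes are smaller: 0.04 and 0.14 for the first two cases.

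**Rejection of a true zero slope** (2,000 simulated trials per cell; Monte Carlo SE about 0.5 points near 5% and 1.1 points near 39%):

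| *d* | Same order, no position | Same order, with position | Separate orders (3 cyclic), no position | Separate orders (all 6), no position |
|---|---|---|---|---|
| 0 | 6.0% | 5.8% | 4.8% | 5.7% |
| 0.25 | 8.3% | 4.5% | 5.7% | 5.1% |
| 0.5 | 39.1% | 5.8% | 4.9% | 5.3% |
| 0.75 | 88.8% | 5.9% | 4.5% | 5.3% |
| 1.0 | 99.7% | 5.3% | 5.0% | 5.7% |

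Repeat simulations, some with other participant-to-residual variance ratios, gave 6.5% to 8.5% at 0.25 SD and 36% to 42% at 0.5 SD.

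**Separate orders, power.** Drift now inflates both within-person variances without adding covariance, so the within-person correlation is multiplied by 1/(1 + d²). From an assumed 0.30:

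- d = 0.5: 0.30/1.25 = 0.24.
- d = 0.75: 0.30/1.5625 = 0.19.

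Simulated power falls from 83-84% without drift to 66-70% at 0.5 SD and 49-53% at 0.75 SD. Position terms for both stages restore 82-84%. Without drift, adding the terms changes power by 1 to 2 points, within simulation error.

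**Relation to the trial's stated power.** The fall from 83% to 68% corresponds to a non-centrality ratio of (1.96 + 0.47)/(1.96 + 0.95) = 0.83. Applied to 97%, (1.96 + 1.88) × 0.83 − 1.96 = 1.23, or about 89% power.

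**The case against.** The strongest objection is that false-positive inflation needs the same, or a positively related, device order at both stages, and the protocol does not establish that. Balanced assignment to three sequences suggests one order per participant. The wording for the emulated session, and what remains of the community-trial sentence, can equally mean a fresh randomisation at each stage. This stands. Separate randomisation by itself prevents the spurious slope, so it would be wrong to say that randomising order without modelling it achieves nothing.

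Several limits on size also stand:

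- No drift is documented. A drift of 0.5 SD per position means 1.0 SD from first to third device. At 0.25 SD the rejection rate is little above the 6.0% the simulation gave with no drift.
- Acclimation and rest between conditions should reduce drift within a session.
- In Aim 2, in-lab fatigue would tend to lower later ratings while adaptation over six weeks would tend to raise them. Opposed drifts push the slope down, against the hypothesis.
- A reader might infer that practice on the performance tests inflates the correlations. It cannot act as a trend in the same measure at both stages: those tests are done with actual AFOs only, and in 2C and 2D they appear only as outcomes, with preference as predictor. A spurious slope there would also need drift in preference.

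Lastly, a statistical analysis plan that is not shown may add period or position terms, and section 4.6 does not exclude them. That tempers the point but does not remove it: the protocol writes a specific model that omits a factor its own design randomises.

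**Conclusion.** The omission is certain on the text; its consequence is conditional. If one device order carries across stages, same-direction drift raises the false-positive rate to about 7-8% at 0.25 SD and about 40% at 0.5 SD per position, and opposed drift biases the slope downward. If orders are drawn separately, the false-positive rate stays near 5% and the harm is lost power: about 84% to 66-70% at 0.5 SD for an assumed within-person correlation of 0.3, or roughly 97% to 89% if the same attenuation is applied to the protocol's own figure. All drift sizes, alpha and the correlation are assumptions.

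A reader might infer that a significant slope in this trial would probably be an order artefact. The documents do not support that: they neither fix a common order nor show a drift. Severity is modest, with high confidence in the omission and conditional confidence in the false-positive consequence.

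**What to change.** In section 4.6, add a categorical fixed effect for position (1, 2, 3) at the stage supplying the outcome to each Aim 1 and Aim 2 model. Where the predictor stage uses a different order, add position at that stage too. Base the slope test on this model.

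In section 4.5, state whether a participant keeps one device sequence across the emulated, actual in-lab and community stages or receives a separately randomised order at each, and complete the description for the actual in-lab and community stages.

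The cost is a sentence or two in each section and 2 degrees of freedom per position factor, so 2 to 4 in all. No new data are needed beyond the order in which each participant tests the devices. If there is no drift, the power loss is negligible.
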